#### 3.2.2. Exclusion criteria

Patients presenting at least one of the following exclusion criteria are not eligible to be enrolled in the study: (a) Severe psychiatric (e.g., psychosis, depression, apathy) and behavioral disorders (e.g., severe psychomotor agitation), cognitive disorders, or a state of confusion defined by temporal and/or spatial disorientation detected during an ordinary conversation. A simple confusion state assessment test (4AT) is administered in case of doubt [42]; (b) Severe upper limb motor deficit with the following score at Motricity Index Scale: gripper <11, elbow flexion <14, shoulder abduction <14 [41]; (c) Verbal comprehension ability with a score of <2 at Token Test [43]; (d) Severe spatial neglect with a score of >3 at Barrage test [44].

### 3.3. Assessment

The basic information, including age, sex, lesion side of the brain, stroke type, and duration after stroke onset, was recorded. The clinical outcomes include motor assessment, which examines the motor function of the patients’ injured upper limb, as well as neuropsychological assessment to evaluate cognitive abilities for the eligibility criteria and to investigate if the rehabilitation program could also impact the patient’s cognition. Additionally, patient’s self-efficacy and satisfaction toward the treatment are also evaluate.

#### 3.3.1. Motor assessment

The *Fugl-Meyer* is subscale included 33-item upper limb activities. Each item was rated on a 0 to 2 ordinal scale. The maximum score of the FMA-UL subscale was 66 [45].The *Motricity Index* for upper limb with a scores ranging from 0 to 100. It evaluated the shoulder abduction, the elbow flexion, and the “grip and pinch” abilities [41].The *Box and Blocks test* which contains 150 wooden cube blocks (1 inch). The participants were told to move one-by-one blocks as many as possible from a rectangular box container to the other of equal size within 60 seconds. Both hands’ scores of the BBT were calculated, respectively, by the number of blocks transferred [46].

#### 3.3.2. Neuropsychological assessment

Proprioception regarding the perception of patient’s body:
Multidimensional Assessment of Interoceptive Awareness (MAIA) [47]: the self-report assesses the following eight interoceptive dimensions: (1) noticing (i.e., tendency to be aware of one’s body sensations, regardless of their (dis)comfort); (2) not-distracting (i.e., tendency to not ignore uncomfortable sensations in the body or pain), (3) not-worrying (i.e., tendency to not worry about uncomfortable sensations in the body or pain); (4) attention regulation (i.e., ability to pay attention to sensations from the body); (5) emotional awareness (i.e., extent to which emotions are perceived as connected to bodily sensations); (6) self-regulation (i.e., ability to use attention to sensations from the body to regulate distress); (7) body listening (i.e., listening actively to the body for insight); and (8) trusting (i.e., degree to which the body is experienced as safe).Thumb Location Test [19] to evaluate the ability of individuals to accurately locate their thumbs without visual cues. During the test, the individual typically closes their eyes or is blindfolded, and the examiner moves the person’s thumb to different positions. The individual is then asked to indicate the location of their thumb by pointing to it with their other hand or verbally describing its position and it is scored from 0 = not accurate to 2 = completely accurate.Rubber Hand Illusion [48] it is a self-report questionnaire that evaluate the participants’ ability to perceive a rubber hand as his/her own in term of ownership, location and agency. The test is administered after the rubber hand induction by a professional with patient’s injury limb. The scale is score from -3 (not at all) to +3 (completely).The Short screening test for ideo-motor apraxia (STIMA) [49] based on the presentation of separated lists of intransitives 18 meaningfulness gestures and 18 meaninglessness gesture score from 1 when the participant successfully imitates on the first attempt, and 2 at the second.The Raven progressive matrices [50] to measure the patient’s abstract reasoning and non-verbal intelligence. It consists of a series of visual pattern problems, where participants are asked to identify the missing piece that completes a pattern.The Trials Making Test (A and B) [51] to evaluate patient’s attention. It is composed of part 1 with a sheet of paper containing circles numbered from 1 to 25. The task is to connect the circles in numerical order as quickly as possible, and part 2 more complex and involves connecting circles that alternate between numbers and letters (e.g., 1-A-2-B-3-C, and so on) in ascending order. The individual is instructed to switch between numbers and letters while connecting the circles.Memory ability:
Corsi Test (visuospatial) [52] used to measure visuospatial short-term memory and spatial span. During the assessment, the participant is presented with a series of blocks, typically arranged in a random pattern and often mounted on a board. The examiner taps a sequence of blocks, and the participant is then asked to reproduce the sequence in the same order. The test progresses in difficulty by increasing the length of the sequences. Performance is typically measured by the longest sequence of blocks that the participant can accurately reproduce.Monaco Test (or digit span forward and backward) [53] to assess the participant’s short-term memory and working memory capacity. It involves the participant repeating sequences of numbers, either forwards or backwards, immediately after they are presented. In the "Digit Span Forward" task, the participant is given a sequence of numbers and is asked to repeat them in the same order. For example, if the examiner says "2, 5, 7," the participant would respond with "2, 5, 7”. In the "Digit Span Backward" task, the participant is given a sequence of numbers and is asked to repeat them in the reverse order. Using the same example, if the examiner says "2, 5, 7," the participant would respond with "7, 5, 2." The test ends when the participant repeats in a wrong way for two consecutive times.Token Test [43] to evaluate the participant’s language comprehension. During the assessment, the participant is presented with a series of commands that involve manipulating tokens (e.g., coins, chips) according to specific instructions. The complexity of the commands gradually increases throughout the test. Performance on the Token Test is evaluated based on the participant’s ability to accurately follow the instructions, manipulate the tokens according to the commands, and demonstrate comprehension of various linguistic concepts such as spatial relationships, object attributes, and logical sequencing.Visuo-spatial ability:
Barrage [44] peripersonal neglect and measure the patient’s spatial and selective attention abilities.Visual object and space perception (VOSP) [54] assessment tool used to evaluate various aspects of visual perception, including object recognition and spatial processing. The test includes “object perception task” that assess the ability to recognize and discriminate between different objects. Examples include matching identical objects, discriminating between similar objects, and identifying fragmented objects; and “space perception task” to evaluate the spatial processing abilities, such as judging the orientation of objects in space, detecting spatial relationships between objects, and perceiving spatial patterns.Self-efficacy state:
Functional Independence Measure (FIM) [55] to evaluate the patients’ self-efficacy after a stroke. The test involves six aspects of daily function: self-care, sphincter control, transfer, locomotion, communication, and social cognition ability. It was made of 18 items, and each item was graded on a 1 to 7 ordinal scale. The total score ranged from 7 to 126.Stroke Self-Efficacy (SSEQ) [56] is a self-report measure designed to assess stroke survivors perceived self-efficacy in managing the various challenges they face during stroke recovery. Self-efficacy refers to an individual’s belief in their ability to successfully perform specific tasks and achieve desired outcomes in a given situation. It is composed by 13 items with a score between 0 = not at all to 3 = completely.Client Satisfaction Questionnaire (CSQ-8) [57], it is a self-report questionnaire that measure the patients’ satisfaction toward the rehabilitation program. It is composed by 8 items ranged from -1 = not at all to +4 = completely.

Table 1 shows the protocol’s assessment.

**Table 1 pone.0307408.t001:** Protocol’s assessment.

Patients’ abilities	Test	Screening (T0)	Pre-test (T1)	Post-test (T2)	Follow-Up (T3)
*Motor*	Fugl Meyer (Platz et al., 2005)		x	x	x
	Motricity Index (Bohannon, 1999)	x			
	Box and Blocks (Mathiowetz et al., 1985)		x	x	x
*Proprioception*	Multidimensional Assessment of Interoceptive Awareness (MAIA) (Mehling et al., 2015)		x	x	x
	Thumb Location Test (Rand, 2018)	x			
	Rubber Hand Illusion (Romano et al., 2021)		x	x	x
*Apraxia*	Short screening test for ideo-motor apraxia (STIMA) (Tessari et al., 2015)		x		
*Intelligence*	Raven progressive matrices (Carpenter et al., 1990)		x		
*Attention*	Trials Making Test (A and B) (Tombaugh, 2004)		x		
*Memory*	Corsi Test (visuospatial) (Piccardi et al., 2013)		x		
	Monaco Test (span forward and backward) (Monaco et al., 2013)		x		
*Language comprehension*	Token Test (De Renzi et al., 1962)	x			
*Visuo-spatial*	Barrage (Albert, 1973)	x			
	Visual object and space perception (VOSP) (Quental et al., 2013)		x		
*Self-efficacy*	Functional Independence Measure (FIM) (Linacre et al., 1994)		x	x	x
	Stroke Self-Efficacy (SSEQ) (Dallolio et al., 2016)		x	x	x
*Satisfaction*	Client Satisfaction Questionnaire (CSQ-8) (Attkisson and Zwick, 2006).			x	

### 3.4. Interventions

The rehabilitation will take place in the rehabilitative room at Bellaria Hospital of Bologna (Italy), which is intended for physical and neurological rehabilitation for people with brain injuries. It is equipped by traditional therapeutic tools and the Virtual Reality apparatus.

#### 3.4.1. Virtual Reality rehabilitation setting

The VR protocol uses two types of technology: three-dimensional (3D) and two-dimensional (2D). During the 3D session, patient sits on a chair and wear the head-mounted display (HMD) while performing some exercises. The exergames consist of tasks requiring precision movements, such as building some blocks, putting the virtual block in a specific position, moving the virtual object inside the environment, paint and colouring some proper figures (Fig 2a). The 2D session is performed by the Virtual Reality Rehabilitation System-Handbox (Khymeia Group, Noventa Padovana, Italy) technology for hand and wrist rehabilitation that tracks the patient’s hand and project it to a monitor without the need to wear any sensor or HMD. Patient sits on a chair, and the monitor screen is positioned at a 1.5 m distance in front of the patient (Fig 2b). Through the Handbox, the patient executes hand exergames based on the pinch, grasp, single finger coordination, wrist movements, customized according to the patient’s motor ability. For both technologies, 3D and 2D, the arm and fingers are captured and projected onto the screen through the Leap Motion Controller. This advanced motion sensor device uses infrared cameras and LEDs to detect and track the position, orientation, and movement of each finger and the hand as a whole. It captures movements at a high frame rate, ensuring smooth and responsive interaction, reproducing an effect similar to the traditional mirror box [58]. For the 3D condition, the Leap Motion Controller is incorporated into the HMD, while for the 2D condition, it is integrated into the Handbox. Both systems allow patients to interact with virtual objects in a natural and intuitive manner. For example, patients can reach out, grab, move, and manipulate virtual objects as they would in the real world. During both sessions, 3D and 2D, there is the constant supervision of the physiotherapist and researcher supervision that guide the patients, directing their focus on the exercises and providing encouragement throughout the tasks.

**Fig 2 pone.0307408.g002:**
[figure not shown]
Experimental setting for VR interventions. (a) 3D—Virtual Reality session; (b) 2D Handbox session.

#### 3.4.2. Experimental treatment

Participants of the experimental group will undergo treatment with Virtual Reality, both IVR and HB. The intervention will consist of 12 sessions lasting about 1 hour each and carried out with a frequency of three days per week within four weeks. Before starting the rehabilitation, arm illusion with the Handbox is inducted to explore the ability of the patients to perceive the virtual arm as their own. During this task, patients sit on a chair with the injured arm inside the Handbox and are invited to perform slow movements with the hand, such as moving the fingers one at a time and moving the wrist up and down. Moreover, they are invited to keep their attention to the virtual arm project on the screen that follows their natural movements. The arm illusion lasts 3 minutes, and the embodiment questionnaire is administered. Then, the treatment starts with IVR and HB sessions (Fig 2), which are counterbalanced to avoid the learning effect. During the IVR, patients sit on a chair and wear the HMD for the immersive experience while performing the abovementioned exercises. During the HB task, patients are sitting on a chair and invited to do some exergames projected on the Khymeia screen, such as inserting pegs into an abacus and pointing some targets, all with the injured arm. All tasks are administered in a complex sequence—the two IVR and HB sessions last half an hour each.

Furthermore, the therapist will establish the facilitation level for each exercise by fine-tuning the sensitivity of kinematic sensors, which range from 1 to 10 based on the patient’s motor impairment. This approach enables patients with minimal hand activity to successfully carry out the exercise. The personalization of exercises is determined by the patient’s baseline hand motor ability. Therefore, individuals with limited hand and arm capabilities will engage in exercises utilizing the Khymeia software’s high movement augmentation score, whereas those with more pronounced hand abilities will perform exercises with a lower augmentation facility score.

#### 3.4.3. Control treatment

Participants randomly assigned to the control group will receive rehabilitation treatment as per usual clinical practice. Specifically, patients will be directed to rehabilitation facilities according to standard clinical rehabilitation pathways. They will be assigned to a physiotherapist who will administer the rehabilitation treatment for the upper limb impairment. Patients in the control group will receive the same amount of rehabilitation for the recovery of upper limb impairment as the treatment group, which means 3 physiotherapy sessions lasting 1 hour 3 times a week for 4 weeks. Based on the treatment intensity, a physiotherapist ensured that the control group received the same level of treatment as the experimental group in terms of the physical effort required by patients.

### 3.5. Outcomes

In assessing the significance of outcome changes, several indicators are utilized. These include the *p*-value, which measures the probability that observed results are due to chance rather than the intervention itself. A *p*-value below a predetermined significance level, often 0.05 or 0.01, indicates statistical significance. Additionally, the confidence interval (CI) provides an estimate of the precision of treatment effects. A narrower CI suggests greater precision in estimating treatment effects. Finally, the Minimal Clinically Significant Difference (MCID) is utilized to assess the significant change perceived by patients regarding the treatment, evaluated through the satisfaction questionnaire.

#### 3.5.1. Primary outcome

The primary outcome measures will be the Fugl-Meyer for Upper Limbs [45] employed as a performance-based assessment to characterize motor recovery in research, has demonstrated outstanding reliability. This encompasses internal consistency, inter-rater reliability, intra-rater reliability, and test-retest reliability, particularly in the post-stroke context [59]. The assessment includes 33 items to evaluate upper extremity motor impairment and is scored between 0 and 2 (0 = unable, 1 = partly able, and 2 = fully able to complete movement) with a total score range of 0–66. The assessment will be performed before treatment (T1), after the conclusion of the treatment (T2), and after 6 months as a follow-up (T3).

#### 3.5.2. Secondary outcome

The secondary outcome will include timed tests that measure the improvement in the Box and Blocks Test [46] for the upper limb ability and motor coordination, MAIA test [47] and the Rubber Hand Illusion [48] for the patients’ proprioceptive ability; the Functional Independence Measure [55] and the Stroke Self-Efficacy [56] for the perceived and real ability in daily life activities. The assessment will be performed before treatment (T1), after the conclusion of the treatment (T2), and after 6 months as a follow-up (T3). Moreover, the satisfaction with the treatment received will also be assessed at T2.

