From a neuroscience standpoint, deficiencies in the planning, preparation, and execution of movements may arise due to impairment in the primary motor cortices or areas responsible for praxis control, particularly those situated in the parietal regions [8–11], which alter proprioceptive and kinaesthetic signals and the perception of peripersonal space [12]. Proprioception refers to the sense of the relative position of one’s own body parts and strength of effort being employed in movement, which can be impaired after a stroke [13]. As a result, patients present distorted body representations and an alteration in the sense of embodiment, in terms of ownership, location, and agency. In particular, people who have survived a stroke experience apparent changes in their bodies, such as altered sensations, impaired limb function, uncoordinated movements and disrupted proprioception [14–16]. Furthermore, sensation, emotions, and perception are some of the characteristics of self-consciousness assimilated into the physical body thanks to the sense of embodiment [17], and that in stroke patients is compromised. The somatosensory deficit that affects this sample of patients refers to an impairment or loss of sensation related to touch, pressure, temperature, or pain on the side of the body affected by the stroke. This deficit occurs due to damage to the brain regions responsible for processing sensory information and patients maintain various delusional beliefs regarding the ownership of their paralyzed limbs [14, 18, 19]. This lack of awareness or recognition of the body can impact the sense of ownership and may lead to difficulties in coordinating movements or adjusting to changes in body perception [20].

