## 2. Objectives and hypothesis

Considering the sensorimotor deficits after a stroke and the relate difficulty to build an internal representation of the own body, plus the significative feature of VR to induce a body illusion, the present protocol aims to investigate the effectiveness of a Virtual Reality rehabilitation program to restore the sensorimotor and proprioceptive abilities of the injured upper limb after a stroke, compared with the treatment as usual (TAU). Moreover, the feature of the exergame of VR would engage the patients and motivate them to pursue the rehabilitation program and overcome the drop-out from the rehabilitation.

### 2.1. Hypothesis 1

VR rehabilitation programs will generally be as effective as TAU in increasing the motor abilities of the injured upper limb after a stroke.

### 2.2. Hypothesis 2

The VR rehabilitation program will be more effective than TAU in the proprioception abilities of the injured upper limb.

### 2.3. Hypothesis 3

The TAU will be the least satisfying rehabilitation program for the patient, with a higher probability of abandonment compared to VR.

### 2.4. Hypothesis 4

The same results will be found across the follow-up assessments (6 and 12 months after intervention).

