#### 3.2.1. Inclusion criteria

Patients must have all the following inclusion criteria: (a) Being 18 to 85 years old, both males and females; (b) Suffering from ischemic or haemorrhagic stroke; (c) The stroke event must have occurred from two to eighteen months before recruitment [40]; (d) Patients must have moderate to severe upper limb motor deficit established by a score of ≤ 80 on the Motricity Index [41], and the alteration of sensorimotor and proprioception abilities of the injury upper limb, established by the failure in 3 proofs up to 4 of the Thumb Location Test [19]; (e) Patients must understand and sign the written consent for enrolment.

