### 3.7. Statistical analysis

The data analysis follows the Per Protocol approach, that is only participants who have adhered to the study protocol, patients who dropped out of the study are excluded from the analysis. Analysis will be performed through the Statistical Package for Social Sciences (SPSS). Descriptive statistics for both the experimental and control groups will encompass measures such as the mean and standard deviation. The student t-test for independent samples will be used to evaluate the baseline. In case of excessive deviation from normality, a similar non-parametric test (Mann-Whitney) will be used. Changes in motor performance and proprioception between T1 and the subsequent longitudinal evaluations (T2, T3) will be assessed using the repeated measures Analysis of Variance (rmANOVA) with a mixed design 2×3, considering the group as "between subjects" factor and the time point measure as "within subjects" factor. Residual plots will be inspected to verify linearity, normality and homoscedasticity assumptions for all models as well as to identify potential influential outliers. According to the literature, for all inferential analyses the probability of type 1 error is a-priori fixed at alpha α = 0.05 and will include reporting the 95% Confidence Interval for each estimate [62].

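### Hypothesis 2 claims better limb proprioception with VR, but no position-sense test is scheduled after screening

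*Protocol article*

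**What the plan says.** Hypothesis 2 (Protocol article, section 2.2) reads: "The VR rehabilitation program will be more effective than TAU in the proprioception abilities of the injured upper limb". The Introduction defines the construct: "Proprioception refers to the sense of the relative position of one’s own body parts and strength of effort being employed in movement".

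Section 3.5.2 names the secondary outcomes that are to carry it: "MAIA test [47] and the Rubber Hand Illusion [48", both assessed at T1, T2 and T3. Section 3.7 plans a 2×3 mixed repeated-measures ANOVA for proprioception over the same three time points.

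A third instrument, the Thumb Location Test, is described in section 3.3.2 as serving "to evaluate the ability of individuals to accurately locate their thumbs without visual cues". Section 3.2.1 relies on it at entry: the sensorimotor and proprioceptive alteration is "established by the failure in 3 proofs up to 4 of the Thumb Location Test". Table 1 marks this test in the Screening (T0) column and nowhere else, and section 3.5.2 does not list it as an outcome.

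**The concern.** The hypothesis concerns an ability of a particular limb. The outcomes assigned to it are two questionnaires, one about awareness of internal bodily sensations and one about an illusion of ownership. Patients are enrolled because they fail a test of position sense, and that test is then never repeated.

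Two errors of interpretation could follow. A better questionnaire score in the VR arm could be reported as better proprioception although limb position sense had not changed. Conversely, a real gain in position sense would go unseen. Proprioception is part of the stated aim of the trial, and Hypothesis 4 carries the same claim into follow-up, so the gap reaches beyond a single secondary comparison.

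**Working it through.** No figure in the plan is in dispute. The check compares what each candidate measure is said to capture with when it is taken.

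| Measure | Described as (3.3.1, 3.3.2, 3.5.1) | T0 | T1 | T2 | T3 |
|---|---|---|---|---|---|
| MAIA | self-report, eight interoceptive dimensions | – | x | x | x |
| Rubber Hand Illusion | self-report, −3 to +3, embodiment of a rubber hand | – | x | x | x |
| Thumb Location Test | performance test, locating the thumb without vision | x | – | – | – |
| Fugl-Meyer (upper limb) | 33 motor items, 0 to 66 | – | x | x | x |

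**MAIA.** The dimensions include not worrying, emotional awareness and trust in the body. None is position sense or effort, and none is specific to the injured limb.

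**Rubber Hand Illusion.** Its location component comes closest in content, but it rates the illusion, not how accurately the patient locates the limb. The article does not say that a stronger illusion means better position sense.

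**Fugl-Meyer.** It cannot fill the gap. With 33 items scored 0 to 2, the maximum is 33 × 2 = 66, which is the stated total, so the motor items account for the whole score and no proprioception score is left over.

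**Thumb Location Test.** It is the only performance measure that fits the position part of the definition. It is taken once, at T0. Of the three time points that the ANOVA needs, it supplies 0 of 3, so no between-group change can be estimated from it.

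**Can the T0 value serve as the baseline if later visits are added?** Not well. Entry requires failure on the test, so T0 values are selected for being poor and some later improvement would be expected in both arms from selection alone.

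**Is the test ready for use as an outcome?** Not yet. Section 3.2.1 counts failures out of 4 trials. Section 3.3.2 gives a score from 0 to 2 and does not say whether this is per trial or overall. The possible scales are:
- failures out of 4: five values (0 to 4);
- one overall score: three values (0, 1, 2);
- if 0 to 2 applies to each of 4 trials and is summed (an assumption): 0 to 4 × 2 = 8.

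All are coarse. If the entry rule means at least 3 failures of 4, T1 scores will probably lie near the poor end.

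**The case against.** **The protocol itself classes the questionnaires as proprioception.** Section 3.3.2 and Table 1 place all three instruments under that label. The Introduction also links disturbed proprioception to altered embodiment, naming ownership, location and agency, which are the three Rubber Hand dimensions. This is a stated reason for measuring embodiment, and embodiment is the proposed mechanism of the treatment. It does not turn an ownership rating into a measure of the ability that the Introduction defines.

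**The Thumb Location Test covers only half of that definition.** This is correct: it addresses position, not effort. It is still the nearest measure in the plan.

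**The full protocol or SAP may deal with this.** Scoring and secondary-outcome analysis may well be left to those documents. The visit schedule is given explicitly in Table 1, however, and no analysis plan can supply observations that were not collected.

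**Hypothesis 2 rests on secondary outcomes.** This stands, and it limits the severity.

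Two stronger readings go further than the documents allow.
- A reader might infer that the VR arm practises the outcome task, because before treatment "The arm illusion lasts 3 minutes, and the embodiment questionnaire is administered". That induction uses a virtual arm and the patient's own slow movements. The outcome follows a rubber-hand induction by a professional, both arms take it at T1, T2 and T3, and the embodiment questionnaire is not identified as the outcome questionnaire. Exposure to a virtual-limb illusion (sections 3.4.1 and 3.4.2) could raise the Rubber Hand score without better position sense. That is a plausible risk, not something shown.
- A reader might count 8 MAIA dimensions plus 3 Rubber Hand components as 11 tests, since "for all inferential analyses the probability of type 1 error is a-priori fixed at alpha" 0.05, and compute 1 − 0.95^11 = 0.431. Nothing in the article says that the components will be tested separately. The figure also assumes independence and is not a ceiling (the Bonferroni bound is 11 × 0.05 = 0.55). It forms no part of this point.

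**Conclusion.** The point holds as a mismatch between hypothesis, outcome and schedule. Position sense is measured by performance at none of the three time points in the planned analysis, and at no time after randomisation. Hypothesis 2 as worded cannot be answered. Comparisons of interoceptive awareness and embodiment remain possible and may be worthwhile under those names.

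The conclusion assumes that Table 1 shows the full schedule for the Thumb Location Test and that the Fugl-Meyer is used as described, as a motor score only. It does not depend on the sample size or on any multiplicity calculation.

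This should be fixed. It is not a defect of the primary analysis, because the Fugl-Meyer outcome and Hypothesis 1 are untouched.

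**What to change.** Preferred change:
1. Reconcile the two scoring descriptions of the Thumb Location Test (sections 3.2.1 and 3.3.2) and state one outcome score.
2. Repeat the test on the injured limb at T1, T2 and T3. The new T1 value is needed because T0 is selected for failure.
3. Name it in section 3.5.2 as the endpoint for Hypothesis 2, compared between arms by a method suited to a coarse ordinal score, for example a proportional-odds model with T1 as covariate. Adjustment may gain little if T1 scores cluster near the floor.
4. Label MAIA as an interoception outcome and the Rubber Hand Illusion as an embodiment outcome.

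If the test is not repeated, reword Hypothesis 2, the matching part of the aim and the eventual conclusions to interoceptive awareness and embodiment, and make no claim about proprioception.

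The first route costs a short extra test per visit, already familiar to staff from screening, and an amended row in Table 1. Its drawbacks are the coarse score and the lack of any measure of effort. The second route needs only a change of text. The choice must be made before follow-up proceeds, because T2 and T3 observations that were not taken cannot be recovered.

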#### 3.5.3. Sample size

A sample size of 30 participants per group has been determined using G*Power 3.1.3. This calculation was based on a repeated measures ANOVAs (within and between subjects), considering a small to medium effect size of 0.2 [60], as also reported in a two-arm Randomized Control Trial involving chronic stroke participants that also adopted as primary outcome measure the Fugl-Meyer scale [61]. The sample size determination also accounted for 20% attrition, with a significance level (α) set at 0.05 and a desired statistical power of 0.80, as outlined in the literature [62]. Additional, participants will be enlisted in the event of any dropouts.

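### Satisfaction is scheduled only at T2 and dropouts are excluded, so the satisfaction half of Hypothesis 3 rests on completers and may be biased

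*Protocol article*

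**What the plan says.** Hypothesis 3 (section 2.3) makes two predictions in one sentence: "The TAU will be the least satisfying rehabilitation program for the patient, with a higher probability of abandonment compared to VR". The introduction to section 2 adds a mechanism: the game-like character of VR should engage patients and keep them in rehabilitation.

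The only satisfaction measure is the CSQ-8. Section 3.5.2 states: "Moreover, the satisfaction with the treatment received will also be assessed at T2". Its row in Table 1 carries a single mark, which agrees with that sentence. Sections 3.5.1 and 3.5.2 place this assessment "after the conclusion of the treatment (T2"). No satisfaction score is scheduled at discontinuation.

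Section 3.7 adopts a per-protocol analysis in which "patients who dropped out of the study are excluded from the analysis". Section 3.5.3 says "The sample size determination also accounted for 20% attrition", gives no split by arm or by period, and adds: "Additional, participants will be enlisted in the event of any dropouts".

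**The concern.** Hypothesis 3 expects the two arms to lose different proportions of patients, and to lose more in the arm expected to satisfy less. A comparison of those who stay is then no longer a comparison of the groups as randomised. If the patients who leave tend to be the less satisfied ones, TAU completers look more satisfied than TAU patients as a whole, and the schedule works against the hypothesis it serves.

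Two features make this more than an analysis detail. A score that was not collected cannot be recovered later by any choice of analysis set. And replacing dropouts adds scores mainly from people who stay, not from those who left. Section 3.5 also uses the satisfaction questionnaire to judge the change that patients perceive, so that judgement would rest on the same selected group.

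**Working it through.** **Inputs from the protocol article.** CSQ-8 at T2 only (3.5.2, Table 1). Dropouts excluded (3.7). Attrition 20% overall (3.5.3). Sample size: "A sample size of 30 participants per group has been determined using G*Power 3.1.3", so 60 in total, 1:1. The article gives no CSQ-8 standard deviation, expected satisfaction difference or attrition by arm, so there is no figure of its own to reproduce on this point.

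**Assumptions.** Leavers score g = 0.5 to 1 SD below completers, with the same gap in both arms. All 20% attrition falls before T2. The split between TAU and VR is 25%/15% or 30%/10%; each averages 20%.

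**Formula.** Let C be the completers' mean in an arm and p its abandonment rate. The mean of all randomised patients is (1 − p)C + p(C − g) = C − pg. The completers' mean is therefore too high by pg, and the VR − TAU contrast in completers is understated by g × (p_TAU − p_VR).

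| Split TAU/VR | g = 0.5 SD | g = 1 SD |
|---|---|---|
| 30%/10% | 0.5 × 0.20 = 0.10 | 1 × 0.20 = 0.20 |
| 25%/15% | 0.5 × 0.10 = 0.05 | 1 × 0.10 = 0.10 |

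**If only half the attrition falls before T2** (15%/5%, assumed): 0.5 × 0.10 = 0.05 to 1 × 0.10 = 0.10 SD.

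**Cross-check with a different model.** Take satisfaction as normal with SD 1 and a true VR − TAU difference d. Let the chance of leaving fall with satisfaction by the same rule in both arms, with 20% leaving overall. For d = 0.5 (assumed):

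| Dependence of leaving on satisfaction | Leavers TAU/VR | Completers' difference (SD) |
|---|---|---|
| none | 20.0%/20.0% | 0.500 |
| logistic slope 0.5 | 21.9%/18.1% | 0.482 |
| slope 1 | 23.4%/16.6% | 0.445 |
| slope 2 | 25.2%/14.8% | 0.381 |
| slope 5 | 26.4%/13.6% | 0.318 |
| hard threshold | 26.8%/13.2% | 0.296 |

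The shrinkage is 4% to 41% of the true difference. Power of a two-sided 5% comparison from 30 per arm is 0.49 if everyone is scored, 0.41 after random 20% loss, and 0.40 down to 0.28 in completers (slopes 0.5 to 5).

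**When the sign changes.** With different gaps the understatement is g_TAU × p_TAU − g_VR × p_VR. If TAU loses 25% for reasons unrelated to satisfaction and VR loses 15% who are 1 SD less satisfied, it is 0 × 0.25 − 1 × 0.15 = −0.15: the VR advantage is overstated by 0.15 SD. In the second model, the difference inflates to between 1.07 and 1.36 times d when dissatisfied VR patients leave more often than TAU patients.

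**Scale against sampling error.** A 20% loss leaves 0.8 × 30 = 24 per arm. The standard error of the difference is then √(2/24) = 0.29 SD; with 30 per arm after replacement it is √(2/30) = 0.26 SD. The largest bias in the first table, 0.20 SD, is below either.

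**Patients affected.** 0.20 × 60 = 12 if all attrition precedes T2; 6 if half does.

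**The case against.** The strongest reply is that the article nowhere says a patient who stops sessions is barred from the T2 assessment. Stopping treatment and leaving the study are different events, and the handling of those who stop is a detail that a full protocol may settle. This is fair as far as data collection goes. It does not rescue the comparison, because section 3.7 keeps only patients who adhered and removes dropouts, so a score obtained from a leaver would be discarded.

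A second reply concerns direction. A reader might infer that Hypothesis 3 itself says the leavers are the dissatisfied patients, so that the contrast must shrink towards zero. It does not: it compares arms, not individuals. Section 5 names other reasons for stopping, including schedule burden, clinical complications and technical problems, and one specific to VR, cybersickness. This objection stands, and the shrinkage is therefore stated only as a conditional result.

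Third, the 20% is a sample-size allowance in a study with follow-up months after treatment. Patients lost after T2 have already had their CSQ-8 assessment. This also stands and makes 0.20 SD and 12 patients upper figures within the assumed range.

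**Conclusion.** The point holds in a limited form. As written, the satisfaction comparison is made among completers only, in a trial that itself predicts unequal abandonment. Under a common leaver-completer gap of 0.5 to 1 SD and more abandonment in TAU, the contrast is understated by about 0.05 to 0.20 SD if all attrition precedes T2, and by less otherwise. The bias can be nil or reversed, and the article's figures cannot show which applies.

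A reader might go further and conclude that a null satisfaction result would be uninterpretable. The numbers do not support that: the bias is below one standard error, and power at d = 0.5 would be only 0.49 with every patient scored, so a null would be weak evidence in any case. The primary outcome is not affected by the CSQ-8 schedule. The change is still worth making, because a named hypothesis depends on this measure, the missing scores cannot be recovered afterwards, and the remedy is cheap.

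**What to change.** 1. In section 3.5.2 and Table 1, schedule the CSQ-8 at T2 or when a patient stops treatment, whichever comes first, and record the reason for stopping.
2. In section 3.7, state that satisfaction and abandonment are compared in all randomised patients with available data, as an explicit exception to the per-protocol exclusion. Without this, the new scores would be dropped and abandonment could not be compared at all, since those who abandon would be outside the analysis set.
3. Keep the completers-only satisfaction comparison as a sensitivity analysis.

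The cost is one 8-item form for each patient who stops: at most about 12 of 60 at the stated attrition, not counting replacements. Some patients will refuse, and scores from those who stop reflect a partial programme, so the report should show them separately as well as pooled.
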